#### Secondary outcomes

At the baseline and at the end of the study, serum concentrations of glucose, total cholesterol (TC), high density lipoprotein (HDL-C), low density lipoprotein (LDL-C), and triglyceride (TG) will be determined by an auto-analyzer. Serum levels of insulin will be also measured by ELISA.

Moreover, insulin resistance will be evaluated at the baseline and at the end of trial by the following two methods:Homeostasis model assessment – insulin resistance (HOMA-IR) = fasting insulin (μU/ml) × fasting glucose (mg/dl)/405.Quantitative insulin sensitivity check index (QUICKI) = 1/log fasting insulin (μU/ml) + log fasting glucose (mg/dl).

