
## Methods

### Design and aim study

This double-blind randomized parallel clinical trial will be carried out at the Department of nutrition, School of Public Health, Shahid Sadoughi University of Medical Sciences, Yazd, Iran. The main aim of this research is to investigate the effect of a 12-week supplementation with total anthocyanin-base standardized cornelian cherry fruit extract on liver function (Serum levels of AST, ALT and CK-18 M30; steatosis and fibrosis of liver), TNF-α, MDA, and adiponectin in patients with NAFLD. (Fig. 1 and Table 1). Moreover, serum concentrations of glucose, total TC, HDL-C, LDL-C, TG, insulin, and insulin resistance will be assessed as the secondary outcomes.

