### Study population

Patients with NAFLD will be selected based on the inclusion and exclusion criteria from gastroenterology clinics affiliated to Diabetes Research Center and Shahid Sadoughi University of Medical Sciences, Yazd, Iran. The inclusion criteria will be having 25–65 years of age; ALT levels of higher than 30 U/L in men and higher than 19 U/L in women; diagnosis of the disease by a gastroenterologist; and grade 1, 2, and 3 fatty liver. Furthermore, patients should be residents of Yazd city and will be required to sign the written consent forms to participate in the research. In the current research, nonalcoholic steatohepatitis (NASH) will be defined based on the guidelines of American Gastroenterological Association and American Association for the Study of Liver Diseases [54]. According to this guideline, NASH is defined as the presence of hepatic steatosis proved by ultrasonography or inflammation with hepatocyte injury (ballooning) with or without fibrosis [54]. Moreover, NAFLD will be diagnosed by ultrasonography based on following criteria: an increase in hepatic echogenicity via renal echogenicity as a reference, presence of enhancement and lack of differentiation of periportal, and bile duct walls reinforcement due to great hyperechogenicity of the parenchyma [55]. Exclusion criteria will include: having any history of diseases such as cirrhosis, viral hepatitis, cardiovascular disease, diabetes, Wilson, and cancer; taking medications including corticosteroids, non-steroidal anti-inflammatory drugs, hypoglycemic agents, or any medicines that affect the blood glucose, tamoxifen, sodium valproate, methotrexate, amiodarone, anti-retroviral agents for HIV, probiotics; consuming any medicine or supplement that affect liver function as well as supplements with antioxidant and anti-inflammatory properties (such as vitamin D, vitamin E, omega-3, resveratrol) one month before the study; following a special diet one month before the study; being pregnant and breastfeeding; and consuming alcohol. We will also ask the patients to not consume the medicines in exclusion criteria list during the study. Moreover, data of the patients with any of the following conditions will not be analyzed at the end of study: patients who take less than 80% of the administered extract or placebo as well as participants who are under a special treatment due to a specific medical reason during the study.

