### Sample size

To estimate the sample size, we considered 95% confidence interval; 80% power (α = 0.05 and β = 0.2); the changes of ALT levels in intervention group compared with the control group, and S = 24% to achieved the significance level of 16% in both study groups according to the study by Zhang et al. [42]. Therefore, the sample size was calculated as *n* = 36 for each group. Eventually, 40 patients will be recruited for each group considering the possible 10% loss.

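### The QUICKI formula is printed without brackets around the sum, so its glucose term runs the wrong way and the index can contradict HOMA-IR

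*Protocol article*

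**What the plan says.** Under Design and aim study, the protocol article places insulin resistance in the second tier: "insulin, and insulin resistance will be assessed as the secondary outcomes". Under Secondary outcomes it adds that "insulin resistance will be evaluated at the baseline and at the end of trial by the following two methods", and gives two formulas:

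- HOMA-IR: "HOMA-IR) = fasting insulin (μU/ml) × fasting glucose (mg/dl)/405".
- QUICKI: "Quantitative insulin sensitivity check index (QUICKI) = 1/log fasting insulin" (μU/ml), followed by a plus sign and "log fasting glucose (mg/dl").

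The QUICKI line has no bracket around the two logarithms and does not state the log base. No other section restates or corrects the formula, so this is the article's only definition of the index.

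**The concern.** By ordinary operator precedence, the printed expression is [1/log(insulin)] + log(glucose). An index of insulin sensitivity should fall as resistance rises. Here the glucose term makes it rise. At fixed insulin, higher glucose scores as more resistant on HOMA-IR and as more sensitive on QUICKI, although the article offers both as measures of the same thing.

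The Statistical analysis section says the analysis will be run in SPSS. If the expression is typed there as printed, the trial would report a quantity that is not a sensitivity index, on a scale several times too large, and its group comparison could disagree in direction with HOMA-IR for no biological reason.

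**Working it through.** The article states no QUICKI value, so there is no figure of its own to reproduce. The check compares the two formulas in the article with each other and with the bracketed form.

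**Inputs.** The formulas come from Secondary outcomes. The article gives no insulin or glucose values, so those below are assumptions: insulin 3–40 μU/ml and glucose 75–125 mg/dl, the glucose limit reflecting the exclusion of patients with a history of diabetes (Study population). Base-10 logs are also an assumption.

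**Forms compared** (I = insulin, G = glucose)

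- HOMA-IR = I × G/405
- Printed = 1/log I + log G
- Bracketed = 1/(log I + log G) = 1/log(I × G) = 1/log(405 × HOMA-IR)

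Over these ranges the bracketed form always falls as HOMA-IR rises. The printed form has no such link to HOMA-IR.

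**Glucose alone, I = 10**

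| G | HOMA-IR | Printed | Bracketed |
|---|---|---|---|
| 85 | 850/405 = 2.10 | 1 + 1.929 = 2.93 | 1/2.929 = 0.341 |
| 120 | 1200/405 = 2.96 | 1 + 2.079 = 3.08 | 1/3.079 = 0.325 |

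HOMA-IR and the bracketed form both show worsening. The printed form shows improvement.

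**Scale.** At I = 10 and G = 100 the printed value is 1/1 + 2 = 3.00 and the bracketed value 1/(1 + 2) = 0.333, a ratio of 9.0. Over the assumed ranges the printed form runs from about 2.5 to 4.2, the bracketed form from 0.27 to 0.43, and the ratio from 8.3 to 10.8. The ratio varies from patient to patient, so rescaling would not repair the values. With natural logs it would be about 28 to 43.

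**Both inputs changing.** For small changes, the printed form changes by −(change in log I)/(log I)² + (change in log G). The insulin term has the right sign and the glucose term the wrong one. For equal proportional falls the two cancel when (log₁₀ I)² = 1, that is at I = 10. Changes from G = 100:

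| Starting I | Both fall 5%: printed | bracketed | I falls 20%, G falls 5%: printed | bracketed |
|---|---|---|---|---|
| 5 | +0.025 | +0.006 | +0.208 | +0.017 |
| 10 | +0.0005 | +0.005 | +0.085 | +0.014 |
| 15 | −0.006 | +0.004 | +0.054 | +0.012 |
| 20 | −0.009 | +0.004 | +0.040 | +0.011 |
| 30 | −0.012 | +0.004 | +0.025 | +0.010 |

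Every row is a true improvement. With equal falls, the printed form has the wrong sign above an insulin of about 10. With a much larger fall in insulin, it has the right sign throughout. A 5% fall in glucose alone always moves it the wrong way, by −0.022.

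**Whole index.** In simulated cross-sectional data (assumed median insulin 10–20 with 50% coefficient of variation, mean glucose 95–100 with SD 10–12, correlation 0 or 0.3), printed and bracketed values correlate at about +0.79 to +0.89.

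**The case against.** The strongest reply is that this is a dropped bracket, perhaps lost in typesetting or in reading the page: the two list items in that section run together, and a stacked fraction with the sum as its denominator would flatten to this same line. That is possible but cannot be shown. The HOMA-IR formula and the unit brackets in the same section are intact, and the QUICKI line is a complete inline expression. Whatever its origin, it is the only definition the article gives.

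A second reply is that the article cites no source for QUICKI and gives no expected value, so calling the bracketed form correct draws on outside knowledge. This stands in part. What the article alone shows is that an index named for sensitivity should not rise with glucose when HOMA-IR rises too. Bracketing the sum uses every printed term and makes the index a decreasing function of HOMA-IR.

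Third, the harm arises only if the formula is coded as printed. No syntax is shown, and values near 3 rather than near 0.3 might well be noticed. That stands and limits the weight of the point. However, the article states no plausible range, and a between-group p-value would not reveal the error.

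A reader might also infer that the QUICKI outcome as a whole would move in the wrong direction. The formula does not support that: only the glucose term is reversed, and a fall in insulin large enough relative to the fall in glucose still moves the printed index the right way.

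**Conclusion.** The formula is wrong as written. Its glucose term has the wrong direction for a sensitivity index, so it can contradict HOMA-IR in the same section. The index is distorted rather than fully reversed: under base-10 logs, equal proportional falls in insulin and glucose give the wrong net sign only above an insulin of about 10 μU/ml.

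The multiple of about 8 to 11 and the threshold of 10 both assume base-10 logs, and the multiple also depends on the assumed ranges. With natural logs the cancellation point would be where (ln I)² = 1, an insulin of about 2.7, so the distortion would be worse. That the glucose term is reversed depends on none of these assumptions.

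The reach is small: one of two indices for a secondary outcome. HOMA-IR, glucose and insulin as separate outcomes, the primary outcomes, and the ALT-based sample size are unaffected. It should be corrected before analysis, but it does not threaten the trial.

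**What to change.** Print the definition as QUICKI = 1/[log(fasting insulin, μU/ml) + log(fasting glucose, mg/dl)], state the log base (for example base 10), and check that the SPSS syntax computes that expression.

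Once the sum is bracketed, the base only rescales the index by a constant (at insulin 10 and glucose 100, 0.333 in base 10 against 0.145 in natural logs, a factor of 2.30). It then matters for the reported values but not for the direction of any comparison.

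The cost is one pair of brackets, a stated base and one line of syntax to check. Insulin and glucose are measured at both time points anyway, so any values already computed can be recalculated without new data.

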### Statistical analysis

Data analysis will be conducted using SPSS version 24 (SPSS Inc., Chicago, IL, USA). The normality of variables will be evaluated using Kolmogorov- Smirnov test. Qualitative and quantitative variables will be presented as numbers (percentages) and mean ± Standard Deviation (SD) or medians with interquartile ranges, respectively. Then, the Chi-Squared test will be used to compare the qualitative variables between two groups. In addition, the variables with normal distribution will be compared between and within the groups using the independent sample t-test and the paired sample t-test, respectively. However, in order to compare the variables with non-normal distribution between and within the groups, Mann-Whitney test and Wilcoxon test will be applied, respectively. To control the confounding variables, analysis of covariance (ANCOVA) will be used to examine the differences in post-intervention values between the two groups while adjusting for the baseline values and covariates. A *p*-value of < 0.05 will be considered as the statistically significant level.

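### Each outcome is tested several ways under one 0.05 threshold with none named as deciding; baseline-adjusted ANCOVA should be the single deciding test

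*Protocol article*

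**What the plan says.** All of this is in the Protocol article.

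- **Normality check** (Statistical analysis): "The normality of variables will be evaluated using Kolmogorov- Smirnov test". Its result selects the next test.
- **Unadjusted tests if normal:** "the variables with normal distribution will be compared between and within the groups using the independent sample t-test and the paired sample t-test, respectively".
- **Unadjusted tests if not normal:** "in order to compare the variables with non-normal distribution between and within the groups, Mann-Whitney test and Wilcoxon test will be applied, respectively".
- **Adjusted test:** introduced as a way to control confounding, an ANCOVA that "will be used to examine the differences in post-intervention values between the two groups while adjusting for the baseline values and covariates". The covariates are not named.
- **Decision rule:** a p-value "< 0.05 will be considered as the statistically significant level", not attached to any one of these tests.
- **Sample size:** "80% power (α = 0.05 and β = 0.2"), based on "the changes of ALT levels in intervention group compared with the control group, and S = 24% to achieved the significance level of 16" percent. I read the 16% as the difference to detect. The size is 36 per group, raised to 40 for 10% loss.
- **Entry criteria** (Study population): ALT above 30 U/L in men and above 19 U/L in women.
- **Outcomes measurements:** every outcome is measured at baseline and at the end, so the baseline covariate is already collected.

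**The concern.** The same between-group question is answered twice for each outcome, once without and once with baseline adjustment. Each arm is also tested against its own baseline. Nothing says which answer counts, and the unadjusted sentence does not say whether it compares end values or changes. The choice can therefore be made after the results are known.

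The consequence depends on how the gap is filled. If any favourable between-group result may be claimed, the error rate for a single outcome exceeds 5%. If an unadjusted result is taken as the answer, the precision that the collected baseline offers is given up.

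The within-arm tests are a separate hazard. Patients enter because their ALT is raised, so some fall is expected in both arms without treatment. A significant fall in the extract arm is then weak evidence, and so is a fall that is significant in one arm only.

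**Working it through.** **Inputs from the plan:** difference 16%, SD 24%, α 0.05 (taken as two-sided), power 80%, 10% loss. **Assumed, because the article does not give it:** baseline-to-end correlation r of 0.3, 0.5 or 0.7.

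**1. The plan's own figure.** n = 2(1.96 + 0.84)² × (24/16)² = 2 × 7.85 × 2.25 = 35.3, so 36 per group. Then 36/0.9 = 40. Both stated figures reproduce. They correspond to an unadjusted t-test.

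**2. Type I error for one outcome.** I simulated normal data with no treatment effect, 36 per arm, with ANCOVA adjusted for baseline only. Each between-group test alone holds about 5%. If a p-value below 0.05 from either the end-value t-test or ANCOVA is enough, two runs with 10,000 and 40,000 trials per scenario gave:

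| r | 0.3 | 0.5 | 0.7 |
|---|---|---|---|
| 10,000 trials | 6.3% | 7.4% | 8.4% |
| 40,000 trials | 6.3% | 7.5% | 8.2% |

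**3. Power if one test decides, with 24% as the SD of change.** Power = Φ[(16/SD) × √(36/2) − 1.96], where √18 = 4.243.

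- Change t-test: SD = 24.
- End-value t-test: SD = 24/√(2(1 − r)) = 20.3, 24.0, 31.0.
- ANCOVA: SD = end-value SD × √(1 − r²) = 19.3, 20.8, 22.1.

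| r | Change t-test | End-value t-test | ANCOVA |
|---|---|---|---|
| 0.3 | 81% | 92% | 94% |
| 0.5 | 81% | 81% | 90% |
| 0.7 | 81% | 59% | 87% |

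Example, ANCOVA at r = 0.5: 16/20.8 × 4.243 − 1.96 = 1.30, and Φ(1.30) = 90%. Simulation with t reference distributions is up to two points lower: about 80% for change, 91% to 58% for end values, and 93%, 89% and 85% for ANCOVA.

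**4. The other reading of 24%.** If it is the SD of end values, the end-value t-test has 81% throughout. The change t-test has 67%, 81% and 95%, and ANCOVA has 84%, 90% and 98%. ANCOVA is not the weakest test in any case examined.

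**5. Within-arm tests.** With no change in either arm, the chance that exactly one arm is significant is 2 × 0.05 × 0.95 = 9.5%. With an assumed common fall of 0.33 SD in both arms and no treatment effect (r = 0.5), simulation gives 50%.

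For ALT, I simulated regression to the mean under assumed values: log SD 0.5, retest correlation 0.7 to 0.8, population median 25 to 40 U/L, and a paired t-test in U/L with n = 36. An untreated arm shows a significant fall in about 8% to 44% of trials with everyone selected above 30 U/L, and in about 3% to 10% with everyone above 19 U/L.

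**6. The normality switch.** For an assumed log-normal marker (log SD 0.5) and n = 36, Kolmogorov-Smirnov rejects normality in 6% of samples uncorrected and in 55% with the Lilliefors correction. Which test is run would then depend on an option that the article does not state.

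**The case against.** The fairest defence is that ANCOVA is already meant to be the efficacy analysis. It is the only test tied explicitly to post-intervention differences between groups, and the unadjusted sentence could describe baseline, dietary or anthropometric data. On that reading, naming the deciding model is a detail for the full plan. This is plausible, but the text does not say it. ANCOVA appears only as confounder control. The unadjusted sentence covers variables generally and pairs between-group with within-group tests, which fits anything measured twice, outcomes included. The sample size also rests on an unadjusted comparison of ALT change.

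Several stronger readings are tempting, and the article does not support them:

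- **Inflated error and lost power together.** They are alternatives. If either test may count, power is not lost: at r = 0.7 it is 87%, against 85% for ANCOVA alone.
- **Error near 10%.** Adding a change-score t-test gives about 9% to 10%, but the article names no such test.
- **The normality switch itself inflates error.** The simulation had no switch and no Mann-Whitney test. The case against the switch is unreliability.
- **ANCOVA is planned on untransformed U/L.** The article is silent on transformation, so this would be inference. The percent scale of the sample size is a reason to specify the log scale; it does not prove a planned error.
- **Regression to the mean will produce significant falls at a known rate.** The rate depends on population values that the article does not give, and it is small near the women's cut-off. Nothing in the article makes within-arm p-values the evidence of efficacy.

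**Conclusion.** The point holds in limited form. The article fixes parallel tests of one contrast under one threshold and leaves open which decides, although a better single analysis is already planned and needs no new data.

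The size is moderate. The excess error is about one to three percentage points per outcome, and only if either between-group result may be claimed. It is separate from multiplicity across the several primary outcomes. If an unadjusted test decides instead, the shortfall against ANCOVA, with 24% as the SD of change, runs from about 2 points (end values, r = 0.3) to 27 points (end values, r = 0.7).

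These sizes rest on the assumed correlations, on normal data and on adjustment for baseline only. That within-arm tests cannot isolate a treatment effect needs none of these assumptions; only the size of the false signal does. This should be corrected, but it does not invalidate the design.

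**What to change.** In the Statistical analysis section:

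1. State that ANCOVA of the end value on group and baseline value is the single deciding between-group analysis for each outcome, with any further covariates named in advance.
2. Specify log transformation of end and baseline values for skewed markers such as ALT. The result is then a ratio with a 95% confidence interval, that is, a percent difference, which matches the percent scale of the sample size.
3. Remove the Kolmogorov-Smirnov switch and check the model residuals instead.
4. Report unadjusted between-group and within-arm results descriptively, without p-values.

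The cost is wording only, with no added patients, visits or assays. The one drawback is that logged markers are read as ratios and not as differences in their original units.

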## Discussion

Nonalcoholic fatty liver disease is one of the most common chronic liver diseases with an increasing prevalence throughout the world. Since no certain therapy has been found for NAFLD yet, determination of new and effective treatments is one of the substantial challenges of the current researchers. Recently, studies indicated that anthocyanins had some impacts on NAFLD. In addition, the protective effects of cornelian cherry fruit extract, as an anthocyanins-rich source, on liver were reported in animal studies. However, very few clinical trials investigated the impact of anthocyanins on NAFLD and we are faced with paucity of information on the disease and its main limitations. Therefore, further clinical trials with a more comprehensive assessment of important variables related to NAFLD are needed to evaluate the impact of anthocyanins on patients with NAFLD. Therefore, we will examine the effect of supplementation with total anthocyanin-base standardized cornelian cherry fruit extract on liver function, TNF-α, MDA, and adiponectin in NAFLD patients. The findings of this study can provide new information over the impact of total anthocyanin-base standardized cornelian cherry fruit extract, as an anthocyanins-rich source, on NAFLD. It also paves the way to discover new approaches for treatment of the disease.

## Data Availability

Not applicable.

## Abbreviations

ALT: Alanine aminotransferase
AST: Aspartate aminotransferase
BMI: Body Mass Index
CK-18 M30: Cytokeratin-18 fragment M30
ELISA: Enzyme-linked immunosorbent assay
HDL-C: High density lipoprotein
HOMA-IR: Homeostasis model assessment – insulin resistance
IPAQ: International Physical Activity Questionnaire
LDL-C: Low density lipoprotein
MDA: Malondealdehyde
NAFLD: Nonalcoholic fatty liver disease
QUICKI: Quantitative insulin sensitivity check index
SD: Standard Deviation
TC: Total cholesterol
TG: Triglyceride
TNF-α: Tumor necrosis factor α
